# Sustained employability of workers in a production environment: design of a stepped wedge trial to evaluate effectiveness and cost-benefit of the POSE program

**DOI:** 10.1186/1471-2458-12-1003

**Published:** 2012-11-20

**Keywords:** Sustained employability, Functional capacity evaluation, Workers’ health surveillance, Stepped wedge trial, Production environment

## Abstract

**Background:**

Sustained employability and health are generating awareness of employers in an aging and more complex work force. To meet these needs, employers may offer their employees health surveillance programs, to increase opportunities to work on health and sustained employability. However, evidence for these health surveillance programs is lacking. The FLESH study (Functional Labour Evaluation for Sustained Health and employment) was developed to evaluate a comprehensive workers’ health promotion program on its effectiveness, cost-benefit, and process of the intervention.

**Methods:**

The study is designed as a cluster randomised stepped wedge trial with randomisation at company plant level and is carried out in a large meat processing company. Every contracted employee is offered the opportunity to participate in the POSE program (Promotion Of Sustained Employability). The main goals of the POSE program are 1) providing employee’s insight into their current employability and health status, 2) offering opportunities to improve employability and decrease health risks and 3) improving employability and health sustainably in order to keep them healthy at work. The program consists of a broad assessment followed by a counselling session and, if needed, a tailored intervention. Measurements will be performed at baseline and will be followed up at 20, 40, 60, 80, 106 and 132 weeks. The primary outcome measures are work ability, productivity and absenteeism. Secondary outcomes include health status, vitality, and psychosocial workload. A cost-benefit study will be conducted from the employers’ perspective. A process evaluation will be conducted and the satisfaction of employer and employees with the program will be assessed.

**Discussion:**

This study provides information on the effectiveness of the POSE program on sustained employment. When the program proves to be effective, employees benefit by improved work ability, and health. Employers benefit from healthier employees, reduced sick leave (costs) and higher productivity. The study can expose key elements for a successful implementation and execution of the POSE program and may serve as an example to other companies inside and outside the industry.

**Trial registration:**

The trial is registered at the Dutch Trial Register (http://www.trialregister.nl): NTR3445

## Background

Sustained health takes a prominent place in daily life and work. (Temporary) inability to work optimally due to health problems causes high productivity loss, and poses a great burden on individuals and society [1,2]. This burden is expected to increase, because of an aging workforce [3,4]. Common to a production environment are injuries and diseases related to musculoskeletal disorders (MSDs). Prevalence of musculoskeletal disorders among workers in the meat processing industry is especially high, with percentages of over 90% [5-7]. MSDs may originate from personal factors such as age, genetics, and Body Mass Index [8] or various contextual factors, such as job demands, job design, seasonality and environmental influences [9] or a combination of both.

The growing proportion of older people in the labour force stresses the need for new policies and programs to assure sustainable employability and to decrease the financial burden. Sustainable employability is defined as employees having the opportunity to perform work with preservation of health and wellbeing during their working life, now and in the future [10]. It is considered a multifactorial concept that can be assessed by multiple outcome measures. Commonly used proxies for sustained employment are work ability, productivity and absenteeism [11,12]. For instance, work ability (measured with the Work Ability Index; [13]) was observed to be a strong predictor of sustained employment which means that employees with lower reported work ability are more likely to develop health complaints and retire early [4,14].

To prevent long term sickness and work disability, risk inventory and evaluations (RI&E) have been introduced at the workplace. One of the outcomes of a RI&E is a plan to minimize potential risks for both employee and employer. In 2009 and 2010, the Dutch Labour Inspectorate performed nationwide inquiries at multiple meat processing companies. The main risk factors identified for sustained employability were related to job demands and job design (machine handling, knife handling, repetitive movements, static postures, work pressure), and contextual factors (work on platforms, biologic agents, noise, safety measures) [15,16]. Personal factors, such as age, ethnicity and employment status, were not examined, but may well form a risk factor [8].

To promote sustained employability, workers’ health surveillances (WHS) have been developed with the aim of promoting sustained employability and health, and of reducing medical costs [17]. A WHS program is developed to provide employees insight into their work ability and health status. This may offer them the opportunity to increase their probability of sustained employability and reduce potential health risks. Recently, some job-specific WHSs and job-specific interventions have been reviewed [18]. In the WHSs workers were screened on several health factors. In the interventions physical and psychological training were deployed to improve job performance. The effects of physical interventions were diverse: healthy lifestyle promotion, physical readiness training and resistance and endurance training were effective on job performance; an exercise intervention program was partly effective; respiratory muscle training was ineffective. One psychological intervention (trauma resilience training) proved to be effective on police performance. Kreis and Bodeker [19] observed positive effects of workplace health promotion, which is practically similar to a WHS, on several health risks (smoking, weight control, and physical fitness). They also observed positive cost-benefit ratios of 1:2.5 and higher for workplace health promotion programs and their effect on absenteeism. Occupational health examinations, i.e. the screening part of a WHS, including a functional capacity evaluation (FCE) have also been reviewed [20,21]. Conflicting evidence was observed for the effectiveness of occupational health examinations including FCE on the prevalence of musculoskeletal injuries [20]. These inconclusive results underscore the need for investigation and evaluation of an integral WHS program. Furthermore, an integral WHS program, including physical, mental and integrated interventions, and its effects on sustained employability has not been studied before.

The POSE program (Promotion Of Sustained Employability) was developed using elements from occupational and rehabilitation medicine. Elements from occupational medicine are e.g. WHSs, and interventions aimed at a healthy lifestyle. Elements from rehabilitation medicine are e.g. FCE, and interventions aimed at improved physical capacity. The POSE program offers employees a custom-made risk profile and, if necessary, an intervention plan using an integral approach [10]. The goal is to reduce sickness absence and, hence, reduce inflow of workers into the ‘Dutch law for Work and Income according to work ability’ (WIA), to prevent income reduction, and to increase sustained employability. The FLESH evaluation study (Functional Labour Evaluation for Sustained Health and employment) was developed to provide insight into the effectiveness of this integrated approach on several outcome measures over time.

### Objective and research questions

The purpose of the FLESH study is to evaluate the effectiveness and cost-benefit of the POSE program on work ability, productivity, and sickness absence among employees in the meat processing industry, compared to care as usual (CAU). The secondary aims are to improve perceived psychosocial and physical workload, health status, and vitality. Along with these evaluations a process evaluation will be conducted among employees and other stakeholders. The objective of this paper is to present the study protocol used in the FLESH study in which the following research questions will be addressed:

1) Does the POSE program improve the primary outcome measures work ability, absenteeism and productivity compared to CAU?

2) Does the POSE program improve the secondary outcome measures psychosocial workload, physical workload, subjective health status and vitality compared to CAU?

3) Is the effectiveness of the POSE program influenced by age, program adherence, risk category, or motivation of management?

4) To what extent do the applied methods appeal to the needs of the involved stakeholders (intervention acceptability)?

5) Is the implementation of the POSE program cost beneficial from the employers’ perspective?

## Methods/design

The CONSORT statement was used in order to describe the design of this study [22,23].

### Trial design and study participants

This study is designed as a stepped wedge trial with a follow-up of one year. The design is presented in Figure 1. The entire study will be carried out within a large meat processing company in The Netherlands, from January 2012 until August 2014.

**Figure 1 F1:**
[figure not shown]
Trial design.

#### Randomisation

Out of the 15 potentially available plants in The Netherlands, five plants fulfilled the inclusion criteria for the FLESH study. Inclusion criteria were having sufficient employees (n) and having budget for POSE program implementation. The order of inclusion in the study was randomly assigned.

#### Procedure

All contracted personnel (n ≈ 1000) are invited by letter to participate in the POSE program at their plant. Personnel is divided into: 1) production personnel and technical services; 2) facility services; 3) staff and office personnel.

Employees are eligible for the FLESH study when they:

– are contracted personnel.

– perform paid labour for at least 12 hours per week at the meat processing company [24].

– agree to participate in the POSE program.

– provide informed consent to participate in the study.

At T_0_, the employees at all five plants receive a baseline questionnaire. At T_1_, the POSE program is implemented at Plant A, the employees at the other plants serve as a control group and receive a follow-up questionnaire. At T_2_, the POSE program is implemented at Plant B, the program continues at Plant A, and Plant C, D and E serve as the control group, etc. T_0_ until T_5_ are separated by 20 weeks each. T_6_ and T_7_ serve as 6 months and 12 months follow-up measurements, respectively. At every time point, all employees receive a questionnaire consisting of items on the primary and secondary outcomes, as well as covariates (see Figure 1).

Because the POSE program consists of ‘care as usual’, the Medical Ethics Board of the University Medical Centre of Groningen decided that a formal ethical approval of the study protocol was not needed.

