#### Digital questionnaire

Employees are asked to complete an electronic questionnaire before the start of the POSE program. This questionnaire focuses on work ability, health and lifestyle. Employees with limited understanding of the Dutch language are assisted in filling out the questionnaire.

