### Statistical analyses

#### POSE program

The effect of the trial on the primary and secondary outcomes will be analysed using linear (for the continuous outcomes) and logistic (for the binary outcomes) multi-level analyses including a random coefficient for plant and a fixed effect for time. The latter parameter is included to adjust for any potential time effects [52]. All tests will be performed two-sided, assuming an alpha of 0.05.

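### A plant leaves the control group at the wave when POSE starts there, with no lag or transition wave, so the questionnaire outcomes at that wave may be counted as intervention data with little or no exposure behind them

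*Protocol article*

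**What the plan says.** The Procedure section sets out who is control at each wave. For the first step: "At T_1_, the POSE program is implemented at Plant A, the employees at the other plants serve as a control group". For the second, with POSE starting at Plant B: "the program continues at Plant A, and Plant C, D and E serve as the control group, etc". Plant A is therefore no longer control at T1, nor Plant B at T2, and the closing abbreviation carries the rule to the later plants.

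The starting plant still supplies outcome data at that wave: "At every time point, all employees receive a questionnaire consisting of items on the primary and secondary outcomes".

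Under Intervention, the Digital questionnaire paragraph reads: "Employees are asked to complete an electronic questionnaire before the start of the POSE program". On its content: "This questionnaire focuses on work ability, health and lifestyle". Assessments, counselling and any tailored intervention are the later parts of the program.

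The Statistical analyses section (POSE program) plans "multi-level analyses including a random coefficient for plant and a fixed effect for time". It defines no exposure variable, lag or transition period.

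**The concern.** Monodisciplinary treatment or multidisciplinary rehabilitation can hardly have worked by the wave at which the program is only being introduced. If the questionnaire at that wave comes before the assessments, the plant's data are CAU data. Placing them on the intervention side mixes untreated observations into the treated group.

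In a stepped wedge model with wave effects and a random plant effect, the cells at the crossover carry most of the weight of the treatment estimate, so the dilution is much larger than the number of affected cells suggests. Work ability is a primary outcome and the only one with a sample size calculation. An effective program could be reported as ineffective.

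**Working it through.** **Inputs.** From Sample size: SD 7.0, ICC 0.034, difference of 3 WAI points, two-sided alpha 0.05, 44 employees per plant. From Procedure: five plants, one starting at each of T1-T5, eight waves (T0-T7). From the Abstract: seven measurements. Assumptions: 44 respondents per plant-wave, equal plants, independent respondents across waves, one constant effect.

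Variance components: τ² = 49 × 0.034 = 1.666 between plants; σ² = 49 × 0.966 / 44 = 1.0758 for a plant-wave mean.

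**The plan's own figure.** The Hussey-Hughes variance is Iσ²(σ² + Tτ²) / [(IU − W)σ² + (U² + ITU − TW − IV)τ²]. Here U is the number of exposed cells, W the sum of squared wave totals and V the sum of squared plant totals. For 4 plants and 5 waves, U = 10, W = 30, V = 30:
- Variance = 4 × 1.0758 × 9.4058 / (10 × 1.0758 + 30 × 1.666) = 40.475 / 60.738 = 0.666, so SE = 0.816.
- Power for 3 points = Φ(3/0.816 − 1.96) = 0.96.

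For 0.90 power this layout needs 34-35 per plant-wave, so the stated 44 is not reproduced exactly; read per wave it is conservative. That does not bear on this point.

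**Attenuation.** Let X be exposure coded from the implementation wave and Z exposure from the next wave. If the true effect follows Z but the model uses X, the expected estimate divided by the truth is B(X,Z)/B(X,X). B is the denominator bracket above with squares replaced by cross-products.

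Five plants, eight waves:
- B(X,X), with U = 25, W = 105, V = 135: (125 − 105)σ² + (625 + 1000 − 840 − 675)τ² = 20σ² + 110τ² = 204.78.
- B(X,Z), with 20 shared cells, cross-products 90 (waves) and 110 (plants): (100 − 90)σ² + (500 + 800 − 720 − 550)τ² = 10σ² + 30τ² = 60.74.
- Ratio = 60.74 / 204.78 = 0.297.

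| Layout (5 plants, n = 44) | B(X,Z) | B(X,X) | Ratio | 3 points read as |
|---|---|---|---|---|
| 8 waves (Procedure) | 10σ² + 30τ² | 20σ² + 110τ² | 0.297 | 0.89 |
| 7 waves (Abstract) | 10σ² + 20τ² | 20σ² + 90τ² | 0.257 | 0.77 |
| T0-T5 only | 10σ² + 10τ² | 20σ² + 70τ² | 0.198 | 0.59 |

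With eight waves and intervention coding, SE = √(5 × 1.0758 × 14.404 / 204.78) = 0.615. Power falls from 0.998 to Φ(0.89/0.615 − 1.96) = 0.30.

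**Sensitivity, no effect at the implementation wave.**
- Eight waves: 0.284 at n = 100, 0.279 at n = 170. At n = 44: 0.34 with ICC 0.01, 0.28 with ICC 0.10, and 0.28 if answers of the same person correlate 0.5-0.7 across waves.
- Extremes: 0.16 (T0-T5 only, n = 200) and 0.50 (ICC 0).

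**Partial effect f at the implementation wave.** Ratio = 0.297 + 0.703f (eight waves, n = 44): 0.47 at f = 0.25, 0.65 at 0.5, 0.82 at 0.75, 1.00 at 1. At f = 0.5 the seven-wave and T0-T5 layouts give 0.63 and 0.60.

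**Three ways to handle the implementation wave (eight waves, n = 44).**

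| Handling | f = 0 | f = 0.5 | f = 1 | SE |
|---|---|---|---|---|
| Intervention | 0.297 | 0.648 | 1.00 | 0.615 |
| CAU | 1.00 | 0.648 | 0.297 | 0.615 |
| Excluded | 1.00 | 1.00 | 1.00 | 0.786 |

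Power with exclusion = Φ(3/0.786 − 1.96) = 0.97.

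**The case against.** A reader might infer that the planned model will report only about 30% of the true effect. The article does not support that as a flat statement, for four reasons.

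- Nothing says that the pre-program questionnaire is the wave questionnaire. It is described as part of the intervention and covers lifestyle, which the outcome list does not name. The two may be one form or two, and the order of the wave form and the program within the implementation wave is not given.
- The coding of the exposure variable is not stated. It follows from who serves as control, but exposure coding is often left to an analysis plan, and the design figures are not shown.
- The 30% needs no effect at the implementation wave, the full constant effect from the next wave, intervention coding and eight waves. The Abstract's seven measurements give a different figure.
- Questionnaire timing cannot touch absenteeism, a primary outcome taken from the occupational health service.

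Fixed CAU coding is no safe remedy either: if the wave questionnaire follows full exposure, it produces the same 0.297.

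All of this stands and makes the size conditional. It does not remove the point. The Procedure states an allocation, and that allocation takes a plant out of control at the wave when the program is only being introduced, with no lag anywhere.

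**Conclusion.** The concern holds as a conditional one. As written, the allocation removes a plant from control at its own implementation wave, while that wave's questionnaire may precede the program or fall at its very start. If these cells are analysed as intervention and carry no effect, the WAI estimate is roughly 20-30% of a constant true effect under the plan's SD and ICC. With half the effect present it is about 60-65%. If the questionnaire follows full exposure there is no bias.

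Two links are inferences: that the wave form is completed before POSE, and that the cells are coded as intervention. The conclusion concerns the questionnaire outcomes (WAI, QQ and the secondary outcomes), not registry absenteeism.

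**What to change.** - For the questionnaire outcomes, define each plant's implementation wave as a transition wave, exclude it from the primary treatment contrast, and count the plant as exposed from the next wave. Under a constant later effect this is unbiased whatever the timing. It needs no new data. The cost is the rise in SE from 0.615 to 0.786 (eight waves, n = 44).
- State whether the wave questionnaire at the implementing plant is completed before or after POSE starts. If before, code that wave as CAU instead; the SE then stays at 0.615.
- For registry absenteeism, split person-time at each plant's actual start date.
- Reconcile the seven measurements in the Abstract with T0-T7 in the Procedure, since the number of waves after the last plant starts changes both the bias and the precision.

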### Intervention

Before the start of the POSE program, employees provide their informed consent for participating in the study. The POSE program consists of assessments and a counselling session. When individual results indicate an increased risk for health problems or absence, an intervention program is offered. An overview of the POSE program is provided in Figure 2.

**Figure 2 F2:**
[figure not shown]
Design of the POSE program within the company.

#### Digital questionnaire

Employees are asked to complete an electronic questionnaire before the start of the POSE program. This questionnaire focuses on work ability, health and lifestyle. Employees with limited understanding of the Dutch language are assisted in filling out the questionnaire.

#### Biometric measurements

Standard biometric measurements are performed on the following parameters: body length, weight, fat percentage, waist circumference, blood pressure, lung function, and cholesterol and glucose levels. Also a hearing test and visual test are administered. These measurements are performed by a physician assistant (PA).

#### Functional capacity evaluation

Before the start of the FCE, employees fill out the Physical Activity Readiness Questionnaire (PAR-Q) [25]. If at least one question is answered positively, employees are not allowed to perform the tests of the FCE that involve peak aerobic and strength capacity. Employees are also not allowed to perform these tests when resting systolic blood pressure exceeds 159 mmHg or resting diastolic blood pressure exceeds 100 mmHg [26]. Depending on the job of an employee, a FCE is performed adjusted to the employee’s job demands. Five domains of functional capacity (material handling, postural tolerance, coordination and repetition, hand and finger strength, and energetic capacity) are tested. Exact procedures have been described elsewhere [26]. The sub maximal Åstrand cycle ergometer test is used to evaluate energetic capacity [27]. The FCE is administered by registered vocational physiotherapists. The physiotherapists receive a one-day training by a licensed trainer, specifically for this study.

#### Counselling session

The employee receives feedback on his/her results from the assessments by a consultant (in most cases the physiotherapist) and advice on whether or not to take consecutive actions. When an employee is advised to take consecutive actions he/she is encouraged to enrol in one of the pre-specified interventions. Depending on the outcome of the assessments, employees are categorised into three different risk profiles threatening sustainable employability: 1) no or very low risk, 2) low to medium risk, and 3) high risk. These risk profiles are based on guidelines by the Netherlands Society of Occupational Medicine (NVAB) [28-32] and guidelines on cardiovascular risk management [33]. Depending on the risk profile, no intervention, a monodisciplinary or multidisciplinary intervention is advised. For instance, multidisciplinary interventions are advised when sick-leave is involved and musculoskeletal and mental complaints are present.

1) For persons with no or very low risk, meetings focussing on primary prevention are organised where general health principles are presented. The meetings are organised at the company’s plants. During these meetings, several topics are addressed, such as lifestyle (change), workload, work capacity and adjustment latitude. Employees are pointed to organisational activities such as company fitness and canteen policy.

2) Persons with low to medium risk are either offered a monodisciplinary intervention or referred to their general practitioner (GP). The intervention can be deployed by a physiotherapist, a psychologist or a dietician. The choice of discipline and the contents of the intervention depend on the outcomes of the assessments, e.g. physiotherapy in case of MSDs. Basically, the interventions are aimed at preserving or restoring functional capacity of the employee, but they can also be aimed at the (work) environment, i.e. at creating and utilizing adjustment latitude. In the present study three ‘physical’ interventions and two ‘non-physical’ interventions are offered: improving personal work capacity, reducing and preventing back complaints, reducing and preventing neck and shoulder complaints, guidance by a dietician in case of substantial overweight of an employee, and stress reduction. These interventions were based on evidence described in several reviews [34-37].

3) Employees with more complex or multiple complaints, who are absent from work regularly or continuously, are offered a multidisciplinary intervention. These multidisciplinary rehabilitation (MR) programs are conducted by professionals from several disciplines, such as a rehabilitation physician, physiotherapists, occupational therapists, and psychologists. Disciplines are deployed on indication. MR is deemed the most preferred evidence-based intervention for chronic complaints of the musculoskeletal system [38]. MR also integrates interventions to adjust the workload, such as job control possibilities.

